### **2. Information/Education**

The education and patient information sheet is attached

## **V. Medical care**

The medical care of the patients is done by [name]. [name] and [name] from the Department of Ophthalmology of the Klinikum Chemnitz gGmbH.

## **VI. Interim analysis and criteria for discontinuation**

The therapeutic trial will be finished prematurely, if:

- two of the first five patients do not tolerate the amniotic holder,
- the rate of patient recruitment is inadequate,
- serious, unresolvable problems concerning the quality of the captured data occur,
- unforeseen circumstances occur which do not allow a continuation of the therapeutic trial,
- unacceptable risks and toxicities occur (decision in accordance with a performed new benefit-risk assessment),
- new scientific results during the term of the therapeutic trial do not permit to continue with this therapeutic trial.

The LKP decides on the discontinuation of the clinical trial.

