**6. Procedure of the clinical trial see III****III. Questions to patients and probands**

10 persons are involved in the pilot study.

It is planned to involve the patients starting Feb 2011.

The postoperative observation period amounts one week. Dependent upon compatibility, the postoperative observation period may be extended to 4 weeks.

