### **Assessment of the effectiveness**

The assessment of effectiveness is performed by daily visit of the probands and by assessment of the anterior eye segment. The primary key performance target of the trial refers to the compatibility of the developed amniotic membrane holder.

If the following points are applicable for one week:

- complete eyelid closure is possible,
- ring does not touch the cornea,
- amniotic membrane is clamped firmly in the holder and is located on the cornea,
- no pain or discomfort occurs,

then this will be considered as a success.

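### The limit of two intolerant patients among the first five has no enrolment hold behind it and no stated meaning of intolerance, so it may be met only after patients 6-10 already wear the device

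*Protocol*

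**What the plan says.** Section VI of the protocol lists the grounds for ending the trial early. One is numerical: the trial ends if "two of the first five patients do not tolerate the amniotic holder". The others have no threshold. The one closest to safety is that "unacceptable risks and toxicities occur (decision in accordance with a performed new benefit-risk assessment" has been made. On who decides, the section says "The LKP decides on the discontinuation of the clinical trial".

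Section III gives the sample size, "10 persons are involved in the pilot study", and the length of follow-up: one week, with the addition that "Dependent upon compatibility, the postoperative observation period may be extended to 4 weeks". The holder is removed and the final examination done at Visit 5, on day 7. Earlier checks are at Visits 3 and 4, on days 1 and 3.

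The section on assessment of the effectiveness defines success by four points: lid closure, ring position, membrane position and absence of symptoms ("no pain or discomfort occurs"). It opens with "If the following points are applicable for one week" and closes with "then this will be considered as a success". The section on the secondary target figure makes the assessment of improvement conditional on the holder being well tolerated. Neither section is cited in section VI, and no section says what counts as not tolerating the holder.

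**The concern.** A rule that looks at the first five patients in order to protect the next five works only if the next five wait for the answer. One-week compatibility is known for a given patient at day 7. The protocol does not ask patient 6 to wait for that, so the limit can be met when there is nobody left to spare. Compatibility of the holder is the primary question, and this is the only numerical check on it during the trial.

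The trigger is also undefined. A patient could fail a success point without being judged intolerant. Conversely, a patient could meet all four points and still be judged intolerant, for example because of the conjunctival pressure marks that the risk-benefit assessment names as a possible effect, since these are not among the four points. Two assessors could read the same five patients differently.

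**Working it through.** **Inputs.** From the protocol: 10 patients (section III); limit of 2 among the first 5 (section VI), read as two or more; one-week assessment at day 7 (Visit 5). Not in the protocol: the true intolerance rate *p* and the pace of enrolment. Both are assumed below over a range. The protocol gives no operating characteristics for the rule, so there is no stated figure to reproduce.

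**1. Exposure without a hold.** Suppose one holder is inserted every *d* days. Patients 6, 7, ... then receive theirs *d*, 2*d*, ... days after patient 5. The number inserted before patient 5's day 7 is the count of *k* = 1, ..., 5 with *k* × *d* < 7.

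| Days between insertions (assumed) | Patients 6-10 already treated before patient 5 reaches day 7 |
|---|---|
| 1 | 5 |
| 2 | 3 |
| 3 | 2 |
| 4 to 6 | 1 |
| 7 or more | 0 |

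These are upper values for the overlap. The limit can be met sooner if a second intolerant patient is recognised before patient 5's day 7.

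**2. Chance that the limit is met.** With X the number intolerant among the first five and X ~ Bin(5, *p*), treating patients as independent:

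P(X ≥ 2) = 1 − (1 − p)^5 − 5p(1 − p)^4

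| Assumed *p* | (1 − p)^5 | 5p(1 − p)^4 | Limit met | Limit not met |
|---|---|---|---|---|
| 10% | 0.590 | 0.328 | 0.081 | 0.919 |
| 20% | 0.328 | 0.410 | 0.263 | 0.737 |
| 30% | 0.168 | 0.360 | 0.472 | 0.528 |
| 40% | 0.078 | 0.259 | 0.663 | 0.337 |
| 50% | 0.031 | 0.156 | 0.813 | 0.188 |

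A hold does not change these probabilities. It ensures that, when the limit is met, none of patients 6-10 has yet been treated.

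**3. Worst case after patient 5.** The largest number intolerant without meeting the limit is 1 of the first five plus 5 of the last five, or 6 of 10. Its probability is 5p(1 − p)^4 × p^5 = 5p^6(1 − p)^4. This is largest at *p* = 0.6: 5 × 0.6^6 × 0.4^4 = 0.006. It is therefore below 1% at every rate.

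**4. Extending the same limit to patients 6-10, for comparison.** The chance that at least one block of five meets the limit is 1 − (1 − P(X ≥ 2))². This gives 16, 46, 72, 89 and 96% for *p* = 10, 20, 30, 40 and 50%, against 8, 26, 47, 66 and 81% for the rule as written. Not all of that gain spares anyone. At *p* = 30% the second intolerant patient of the second block is the last patient with probability 4 × 0.3² × 0.7³ = 0.123. That is 0.123 / 0.472 = 26% of the second-block stops, and by then no patient is left to spare.

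**The case against.** Several points against this carry weight. The rule need not wait for patient 5's day 7: it is met as soon as a second intolerant patient is seen, and patients are examined on days 1 and 3. The section on effectiveness even speaks of daily visits. The brief summary in section II says the holder can be taken out at any time. If enrolment is slow, there is no overlap at all. These points reduce the exposure, but they do not close the gap, because the protocol guarantees neither a slow pace nor early recognition.

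Three stronger readings are tempting, and the protocol does not support them.

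- *That 6 of 10 intolerant patients is a realistic outcome under the rule.* It is arithmetically possible, but its probability never exceeds 0.6%.
- *That patients 6-10 have no protection.* Stopping on the first five protects them if the rule is read in time, and the criterion on unacceptable risks and toxicities applies throughout. It is a matter of judgement with no threshold, which is not in itself an error in an open pilot of 10 patients.
- *That intolerance must equal failure of the success definition.* Success includes a technical point, the membrane being firmly clamped and in place, which a patient could fail while tolerating the device. Different terms are no contradiction. What remains is that the relation between them is not stated.

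**Conclusion.** The concern holds in a limited form. The protocol's one numerical stopping limit has no enrolment hold, so between none and all five of the later patients may already be treated when it can be fully evaluated. The number depends on an enrolment pace that the protocol does not give. The situation in which a hold matters is not rare: the limit is met with probability 26% at an assumed intolerance of 20% and 66% at 40%. After patient 5 no numerical limit applies, but the judgement-based criteria do. The trigger is undefined and unrelated to the success points and to the condition on the secondary target.

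The figures rest on assumed intolerance rates, independence between patients, and reading two as two or more. This is a cheap improvement to the conduct of the trial and not a fatal flaw. The absence of a numerical limit for patients 6-10 is a design choice and not counted as an error.

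**What to change.** 1. In section VI, state that patient 6 is not enrolled for treatment until the first five have completed the day-7 assessment and the rule has been checked. If the limit has already been met, the trial ends under the existing rule without waiting. The wording should also say how a patient who leaves before day 7 is handled, and that two means two or more if that is intended.
2. Reconcile the terms in section VI, the section on assessment of the effectiveness and the section on the secondary target figure, so that it is clear how not tolerating the holder relates to the four success points and to being well tolerated. What counts as intolerance is for the sponsor and investigator to decide.
3. Let the sponsor decide, and record, whether a numerical limit should also apply to patients 6-10. Using the same limit there raises the chance of stopping at 10% intolerance from 8% to 16%, and some of those stops would come too late to spare anyone.

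Items 1 and 2 cost protocol wording and a pause of about one week after patient 5.

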## **VII. Take-over declaration for the fee (if desired)**

According to the provisions of the Medicines Act (§ 40 Section 1 No. 4 AMG) and other regulations, the clinical trial of drugs in humans may only be performed, if and as long as it is directed by a physician who has at least a two-year experience in clinical testing of drugs.

[name]. [name] has more than two years of experience in the execution of clinical trials. [name] is investigating physician in the Department of Ophthalmology of the Klinikum Chemnitz gGmbH, and also has more than two years of experience in the execution of studies.
